### Experimental paradigm

The experimental paradigm consists of six computer-generated social scenarios simulating a pedestrian street presented in virtual reality. Within each scenario, one avatar approaches the participant and initiates a 19-second interaction. The scenarios vary along two parameters: social complexity, operationalised as the number of avatars present in the background (0, 5, or 25), and the presence or absence of a non-social distractor (an ambulance in the background).

The virtual environment consists of a pedestrian street featuring elements such as buildings with large shopping windows, benches, and a large tree. The duration of each scenario is 90 seconds. When entering the scenario, participants are positioned centrally within the street, facing the same direction each time. Participants can orient themselves while remaining stationary within the environment, i.e., they are unable to perform any locomotion. In each scenario, after 30 seconds, an interlocutor avatar emerges from a passage to the right of the participant’s initial orientation and approaches them. The interlocutor stops directly in front of the participant, adjusting to account for the participant’s physical orientation within the virtual space. Once stopped, the avatar engages in a 19-second interaction involving an initial, neutral question, a brief pause allowing the participant to respond, and a neutral concluding remark (see Table 1 for an overview of the interactions). Following the interaction, the avatar exits the walking street down a passage located behind the participant’s original physical orientation. The avatars are distinct across scenarios, featuring three male and three female characters. All interacting avatars display consistent conversational body language and attempt to maintain eye contact. The scenario concludes after a total of 90 seconds.

**Table 1 pone.0316502.t001:** Overview of avatar interactions.

Initial question	Response
Hi, I couldn’t help but notice your shoes – they’re really nice! Where did you get them?	Thanks – I’ll have to see if I can find a pair like that.
Hey, could I borrow your phone? I can’t find mine – I think I might’ve left it on the bus.	Oh wait, maybe I left it at the café. I’ll just check.
Excuse me, do you know what time it is? I’ve got to catch my movie at the cinema.	Oh, I’d better hurry – it’s starting soon, and my friends are waiting for me.
Hi, could you point me in the direction of City Hall? It’s my first time here.	I’m so bad with maps; I’ll see if I can figure it out.
Hi! I’m from Animal Protection. Do you have a moment?	Thanks for your time – we’re holding a big event next week. You can read more about it on our website.
Hey there – don’t we know each other? Didn’t we meet at Line’s New Year’s party?	Oh no, I’m sorry! I thought you were someone else – have a great day!

Across the six scenarios, two parameters are manipulated: social complexity and the presence of non-social distractors (see Table 2 for an overview of conditions for each scenario). Social complexity is operationalised as the number of avatars present in the background of each scenario, as this has been found to be a moderating factor when comparing gaze behaviour between ASC and neurotypical groups [31–33]. Three conditions comprise this parameter: *1.* Low social complexity, with no avatars present within the background; *2.* Moderate social complexity, with five avatars walking in the background of the pedestrian street; *3.* high social complexity, with 25 avatars walking in the background on the pedestrian street. The second parameter, non-social distractors, is manipulated through the presence of an ambulance in half of the scenarios, as previous findings suggest that autistic individuals show preferential attention toward non-social objects in a visual scene [46–48].

**Table 2 pone.0316502.t002:** Experimental conditions.

	Non-social distractor absent (Absent conditions)	Non-social distractor present (Present conditions)
**Low social complexity** **(0 background avatars)**	Scenario 1	Scenario 4
**Moderate social complexity** **(5 background avatars)**	Scenario 2	Scenario 5
**High social complexity** **(25 background avatars)**	Scenario 3	Scenario 6

### Apparatus

Stimulus presentation and gaze data collection will be conducted using the HMD Varjo Aero. Stimulus is presented through a high-resolution display of 2880 x 2720 pixels per eye, with a 115-degree horizontal field of view, at a 90 Hz refresh rate. Eye movements are recorded from both eyes at a sampling rate of 200 Hz with sub-degree accuracy. The Varjo Aero utilises a 5-point calibration technique. The HMD is paired with a high-performance PC, through which stimulus is controlled. Experimental stimuli are presented using the *Social World* software developed by CleVR. *Social World* was originally developed as a therapeutic tool in the treatment of various mental disorders, [49] but has been further developed to integrate an eye-tracking system.

### Procedure

Participants from both the ASC and neurotypical groups will be invited to the laboratory, informed about the purpose of the study, and complete an informed consent form. Prior to the experiment, participants undergo clinical assessment by experienced psychologists to ensure eligibility criteria are fulfilled and to collect clinical, cognitive, and behavioural measures (see section Assessment battery) to be included in the statistical analyses.

Following the clinical assessment, participants will proceed to the experimental task and receive verbal instructions about the general nature of the experimental task. Participants will be instructed to respond to the questions posed by the interacting avatars to increase immersion and presence within the task. Between each scenario, participants’ gaze will be calibrated through the 5-point calibration within the HMD to improve the accuracy of data collection. Following the experiment, participants will be debriefed and thanked for their participation.

### Assessment battery

Preceding the experimental task, all participants will undergo an assessment comprised of the following clinical and cognitive measures

### Clinical

Mini International Neuropsychiatric Interview (M.I.N.I), v. 5.0 will be used to assess general psychopathology in order to record any cooccurring psychiatric conditions within the ASC group and to exclude any current psychiatric diagnoses within the neurotypical group [50].Danish Weschler Adult Intelligence Scale (WAIS-IV), subtests Vocabulary and Matrix reasoning, will be used to estimate full-scale IQ to confirm eligibility, which are known to correlate with full-scale IQ [51,52].Social Responsiveness Scale 2 – Adult Version, Self-report (SRS-2A Self-report), will be used to measure degree of social impairment [42].Social Responsiveness Scale 2 – Adult Version, Informant (SRS-2A Informant) will be used to measure degree of impairment as reported by an informant close to the participant [42]- Social Interaction Anxiety Scale (SIAS) [53] will be used to measure levels of social anxiety.Empathy Quotient (EQ) will be used to measure level of empathy [54].- Camouflaging Autistic Traits Questionnaire (CAT-Q) will be used to measure social camouflaging behaviours [12].- Sensory Reactivity in Autism Spectrum questionnaire (SR-AS) will be used to assess degree of sensory reactivity, including both hyperreactivity and hyporeactivity [55].Beck Depression Inventory (BDI) will be used to assess level of depressive symptoms [56].Repetitive Behaviour Questionnaire (RBQ-3) will be used to assess repetitive behaviours, including motor stereotypies, ritualistic behaviours and restricted interests [57].- Adult ADHD Self-Report Scale (ASRS) will be used to assess the severity of ADHD symptomology, including impulsivity-hyperactivity and inattention. [58]

### Social functioning

High Risk Social Challenge Task (HiSoC) is a performance-based measure and will be used to assess social functioning [59].Social Skills Performance Assessment (SSPA) is a performance-based measure and will be used to assess social functioning, including social appropriateness, conversational interest/disinterest and negotiation skills [60].Temple University Community Participation (TUCP) measure will be used to assess frequency and quality of community engagement over the course of the previous 30 days [61].Personal and Social Performance Scale (PSP) is used to assess level of social functioning, assessing functioning in domains including socially useful activities, personal and social relationships, self-care and aggressive or disturbing behaviours [62].

### Social cognition

CANTAB Emotion Recognition Task (CANTAB ERT) will assess the ability to identify emotions in presented images of facial expressions [63].The Assessment of Social Inference Test, Short form, part 2 social inference, minimal (TASIT-S) will assess theory of mind and complex emotion comprehension [64].The Hinting Task will assess theory of mind by measuring the ability to grasp indirect or implied meanings in social communication [65].

### Outcome measures

Outcome measures are gaze behaviour analysed through fixation-based metrics including number of fixations, mean fixation time in milliseconds, and dwell time in milliseconds on predetermined Areas of Interest (AOI). Areas of interest are predefined and categorised as social and non-social stimuli. Within social stimuli, AOIs are further categorised to include head, eye, mouth, forehead, and body regions of avatars. AOIs within non-social stimuli will consist of shopping windows, the ambulance when present, and the remaining background. Exploratory outcome measures are associations between eye movement data and clinical, social functioning, and social cognitive measures.

### Sample size calculation

Sample size was determined a priori based on one of the primary hypotheses of detecting a between-group difference in total fixation duration (dwell time) on the eye regions. The minimal detectable effect size as set at Hedges’ g =  0.47, as established by Frazier et al.’s 2017 meta-analysis [28]. An allocation ratio of 0.35 was selected due to clinical availability to a cohort of participants with ASC [39] and anticipated greater heterogeneity in gaze behaviour within the ASC group [66].

Assuming a two-sided hypothesis with a significance level of 0.05 and statistical power of 80%, the sample size calculation indicated 139 and 48 NT participants. To account for potential attrition, we will recruit 140 ASC and 50 NT participants.

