### Statistical analyses

Data will be analysed using Statistical Package for the Social Sciences (SPSS) and R software for statistical computing. Data analysis will be conducted using mixed design ANCOVA and MANCOVAs combining between-subjects and within-subjects analysis. Initially, a one-way ANOVA will be performed to examine group differences (ASC vs neurotypical) on demographic, clinical, psychosocial, and social cognitive measures. Means, standard deviations and F-scores will be reported.

To examine gaze behaviour across different regions of interest (social vs non-social areas and regions within these categories), MANCOVAs will be conducted with group (ASC vs neurotypical) as the between-subjects factor and AOIs as within-subjects factors. The potential influence of social complexity will be assessed using a MANCOVA with a group (ASC vs neurotypical) as a between-subject factor and social complexity and AOIs as within-subject factors. ASRS score will be included as a covariate to control for potential confounding influences of ADHD symptomology on visual attention.

Exploratory analyses using linear regression will evaluate potential correlations between eye-movement data and clinical, functional, and social cognitive measures.

All statistical tests for significance will be two-tailed and with a significance level alpha set at p < 0.05. Any missing data will be handled using multiple imputation. In the event of non-normally distributed data, appropriate adjustments will be made, such as using corresponding non-parametric tests.

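### The plan expects more variable gaze in the larger ASC group but analyses with models that pool variances, so the group test is conservative; its example fallback would also drop the ASRS covariate

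*Protocol article*

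**What the plan says.** Two sections of the protocol article bear on this.

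- **Sample size calculation.** Two reasons are given for the unequal groups. The first is access to an existing cohort: "An allocation ratio of 0.35 was selected due to clinical availability to a cohort of participants with ASC". The second is "anticipated greater heterogeneity in gaze behaviour within the ASC group". No SD or SD ratio is given. The target effect is a Hedges' g of 0.47 for dwell time on the eye regions, two-sided 5%, with "statistical power of 80%, the sample size calculation indicated 139 and 48 NT participants". The plan then states that "we will recruit 140 ASC and 50 NT participants".
- **Statistical analyses.** "Data analysis will be conducted using mixed design ANCOVA and MANCOVAs combining between-subjects and within-subjects analysis". Group is the between-subjects factor, AOI and social complexity are within-subjects factors, and the ASRS score is a covariate intended to control confounding by ADHD symptoms. The stated contingency is "In the event of non-normally distributed data, appropriate adjustments will be made, such as using corresponding non-parametric tests". Unequal variances are not mentioned.

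**The concern.** The expected difference in spread is used to justify the allocation but is not carried into the analysis. Standard ANCOVA and MANCOVA pool the variance (or covariance matrix) across groups. With unequal group sizes, pooling gives the wrong standard error when the spreads differ. Here the group expected to be more variable is also 140/50 = 2.8 times larger, so the pooled standard error is too large. The between-group comparison of eye-region dwell time, on which the study was sized, would then be less sensitive than the data allow.

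The contingency addresses a different problem, non-normality. Fixation counts and dwell times on small regions are counts or bounded times, so that clause may well be triggered. In their usual form the counterparts (Mann-Whitney, Friedman) carry no covariate and do not reproduce a group by complexity by AOI model. An ASRS-adjusted comparison could therefore become an unadjusted one after the data have been seen.

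**Working it through.** **Inputs from the protocol article:** g = 0.47, two-sided alpha 0.05, power 80%, NT:ASC ratio 0.35, recruited sizes 140 and 50. **Assumption:** the SD ratio k = SD(ASC)/SD(NT), which the article does not give; 1.0 to 2.0 is shown.

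**1. The plan's own figure.** With one common SD, n(ASC) = (1.96 + 0.8416)² × (1 + 1/0.35) / 0.47² = 7.849 × 3.857 / 0.2209 = 137.05, rounded up to 138, and 0.35 × 138 = 48.3 NT. The stated 139 and 48 reproduce within rounding. The exact t-test power is 79.8% at 139/48 and 81.0% at 140/50. The calculation therefore uses equal variances.

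**2. Standard errors at 140/50, with SD(NT) = 1.**

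- Pooled variance: sp² = (139k² + 49)/188
- Pooled SE = sqrt(sp² × (1/140 + 1/50))
- True SE = sqrt(k²/140 + 1/50)

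For k = 1.5: sp² = (312.75 + 49)/188 = 1.924. Pooled SE = sqrt(1.924 × 0.02714) = 0.2285. True SE = sqrt(0.01607 + 0.02) = 0.1899. The ratio is 1.20.

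Type I error below is from simulation (200,000 runs per setting); coverage is from the SE ratio.

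| k | Pooled SE / true SE | Type I error, pooled | Type I error, Welch | Coverage of nominal 95% interval, pooled |
|---|---|---|---|---|
| 1.0 | 1.00 | 5.0% | 5.0% | 95.0% |
| 1.25 | 1.11 | 3.0% | 5.0% | 97.1% |
| 1.5 | 1.20 | 1.9% | 5.0% | 98.2% |
| 2.0 | 1.34 | 0.9% | 5.1% | 99.1% |

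**3. Power.** Once the SDs differ, g = 0.47 needs a reference SD, and the answer depends on it. Simulated power, pooled vs Welch:

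| k | g in pooled-SD units | g in root-mean-square-SD units | g in NT-SD units |
|---|---|---|---|
| 1.25 | 84% vs 88% | 79% vs 85% | 68% vs 75% |
| 1.5 | 85% vs 93% | 78% vs 88% | 54% vs 69% |
| 2.0 | 88% vs 97% | 76% vs 92% | 31% vs 56% |

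Check by normal approximation for k = 1.5 in pooled-SD units: the difference is 0.47 × 1.387 = 0.652, and 0.652/0.1899 = 3.433. The pooled test needs 1.96 × 1.203 = 2.358, so power = Φ(1.07) = 86%. The unequal-variance test needs 1.96, so power = Φ(1.47) = 93%.

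**4. Can hypothesis 3 still be tested by ranks?** Take each participant's contrast, 25 minus 0 background avatars, and compare the groups by Mann-Whitney. This is a rank test of the group by complexity interaction. In an illustrative simulation with skewed data (4,000 runs per setting, assumed shapes), at k = 1 / 1.5 / 2:

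- Mann-Whitney type I error: 4.9% / 3.0% / 2.8%
- Mann-Whitney power: 89% / 76% / 58%
- Pooled t-test power: 72% / 44% / 25%

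The interaction remains testable. The ASRS adjustment and the joint test over AOIs are lost.

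**The case against.** - **Enlarging the more variable group is sound design, and cohort availability is the first reason given.** This stands. The weakness is only that the expected spread goes no further than the allocation.
- **The test errs on the safe side.** This stands. A reader might infer from a wrong standard error that false positives are inflated. That would need the smaller NT group to be the more variable one (type I error 10.3% at k = 0.67), the opposite of what the plan expects.
- **The design target may still be met.** This stands in part. In pooled-SD units the pooled test has more than 80% power at every ratio shown. In root-mean-square units it falls just below (79% to 76%), and in NT-SD units well below. The loss is against a better analysis of the same data, and only on some scalings against the plan's own target.
- **Hypothesis 3 is not lost.** A reader might infer that the fallback makes this interaction untestable. The documents do not support that: the clause is conditional, rank tests are given only as an example, and a rank test on within-person contrasts addresses the interaction.
- **The detail may be in a SAP, and this is a condensed article.** A SAP that is not shown could specify robust methods. The point is therefore limited to what the article states: an expectation in one section, and in another models and a contingency that do not match it.
- **The figures are for an unadjusted comparison of two means.** This stands. They indicate direction and rough size, and do not carry over exactly to ASRS-adjusted or within-person tests.

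**Conclusion.** The mismatch between the two sections is real, and its direction follows from the plan's own expectation. If ASC gaze is more variable, the pooled group test is conservative, its intervals are too wide, and power is given away: 4 to 10 percentage points at k = 1.25 or 1.5 on the first two scalings of g, and 7 to 15 points in NT-SD units. The size rests on an SD ratio that the article does not supply, and if the variances are equal there is no loss. The concern is precision, not validity.

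The fallback is loosely fixed: its named example would, in the usual form, remove the covariate that the plan includes against confounding, and would not reproduce the joint model. Hypothesis 3 would still be testable.

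**What to change.** In the statistical analyses section, before outcome data are analysed:

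1. For the group comparisons, specify either a mixed model with group-specific residual variances (and a group-specific variance for any participant effect), or heteroscedasticity-robust (Welch- or HC3-type) standard errors on participant-level summaries.
2. Replace the non-parametric example by a pre-specified participant-level bootstrap, resampling within group, or a robust version of the same model. The ASRS covariate and the group by complexity interaction then stay in whichever route is taken.

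The cost is slightly more programming in R, which the plan already names, and a small loss of precision if the variances turn out equal: at k = 1, simulated power is 80.7% for Welch against 81.2% for the pooled test. No extra participants are needed.

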### Statistical analyses

Data will be analysed using Statistical Package for the Social Sciences (SPSS) and R software for statistical computing. Data analysis will be conducted using mixed design ANCOVA and MANCOVAs combining between-subjects and within-subjects analysis. Initially, a one-way ANOVA will be performed to examine group differences (ASC vs neurotypical) on demographic, clinical, psychosocial, and social cognitive measures. Means, standard deviations and F-scores will be reported.

To examine gaze behaviour across different regions of interest (social vs non-social areas and regions within these categories), MANCOVAs will be conducted with group (ASC vs neurotypical) as the between-subjects factor and AOIs as within-subjects factors. The potential influence of social complexity will be assessed using a MANCOVA with a group (ASC vs neurotypical) as a between-subject factor and social complexity and AOIs as within-subject factors. ASRS score will be included as a covariate to control for potential confounding influences of ADHD symptomology on visual attention.

Exploratory analyses using linear regression will evaluate potential correlations between eye-movement data and clinical, functional, and social cognitive measures.

All statistical tests for significance will be two-tailed and with a significance level alpha set at p < 0.05. Any missing data will be handled using multiple imputation. In the event of non-normally distributed data, appropriate adjustments will be made, such as using corresponding non-parametric tests.

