### Hypotheses

In line with previous findings [18,28,29,31–33], we hypothesise that:

1) Autistic participants will exhibit fewer fixations and shorter dwell time on eye regions of avatars compared to neurotypical participants across the experimental tasks.2) Autistic participants will exhibit different gaze behaviours, such as fewer fixations and shorter fixation duration (dwell time) on social areas (head and body) of the avatars presented in the virtual reality (VR) scenarios compared to neurotypical participants. Additionally, we hypothesise that the number of fixations, mean fixation and dwell time will be greater on non-social areas (objects and surroundings) among autistic participants across the experimental tasks.3) Increased social complexity across conditions, operationalised as a greater number of avatars present, will result in an increase in the number of fixations, mean fixation time, and dwell time on non-social areas among autistic participants compared to neurotypical controls.

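### Hypothesis 3 predicts a directional rise in non-social gaze over three ordered complexity levels, but the only stated test is an omnibus MANCOVA that ignores order and direction and does not isolate non-social areas

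*Protocol article*

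**What the plan says.** The third hypothesis in the protocol article (Hypotheses) is ordered and directional: "Increased social complexity across conditions, operationalised as a greater number of avatars present, will result in an increase in the number of fixations", and likewise in mean fixation time and dwell time, on non-social areas, in autistic participants compared with controls.

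Experimental paradigm defines the exposure as "social complexity, operationalised as the number of avatars present in the background (0, 5, or 25" avatars, and Table 2 names the levels low, moderate and high. Each level occurs once with and once without the ambulance.

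Statistical analyses assesses the influence of complexity by a "MANCOVA with a group (ASC vs neurotypical) as a between-subject factor and social complexity and AOIs as within-subject factors", with the ADHD symptom score as covariate. The general rule is "All statistical tests for significance will be two-tailed and with a significance level alpha set at p < 0.05". The section names no trend or planned contrast, no model term that decides hypothesis 3, no restriction to non-social areas of interest (AOIs), and no rule for what would count as support.

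**The concern.** The hypothesis makes a claim about direction along an ordered scale, in one class of AOI. The stated test asks whether the groups' profiles over three categories differ in any way. The two can part company in three respects.

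- **Order.** The group-by-complexity F statistic is unchanged if the labels 0, 5 and 25 are permuted. A rise, a fall and a peak at the middle level of the same size are equally detectable.
- **AOI.** A group-by-complexity term averaged over AOIs mixes social and non-social gaze. Scenarios last a fixed 90 seconds and the AOI list includes the remaining background, so dwell time gained on one class is largely lost from the other and the averaged term may show little. The three-way term with AOI can detect a shift between classes, but can also be significant because gaze moved among social AOIs only.
- **Power.** Degrees of freedom are spent on patterns that the hypothesis does not predict.

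At stake is whether a significant result, or the lack of one, can be interpreted for one of three named hypotheses.

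**Working it through.** **1. The plan's own figure.** Sample size calculation uses Hedges' g = 0.47, two-sided alpha 0.05, power 80% and allocation ratio 0.35, for dwell time on the eye regions.

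- ASC: (1 + 1/0.35) × ((1.960 + 0.842)/0.47)² = 137.05
- Neurotypical: 0.35 × 137.05 = 47.97

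The stated 139 and 48 have 79.8% power by the noncentral t and 80.2% by the normal approximation, so the figure reproduces. It does not concern hypothesis 3, for which no effect size or power is stated.

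**2. Assumptions for hypothesis 3.** 140 and 50 participants; alpha 0.05; one outcome, averaged over the distractor conditions; equal variances and correlations across levels; no allowance for the covariate. Because no effect size is given, the noncentrality λ is anchored to the power of the trend contrast.

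- Trend contrast (group × scores −1, 0, 1): F with 1 and 188 df
- Omnibus group × complexity: F with 2 and 187 df

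**3. A linear rise (all of λ lies in the trend).**

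| λ | Trend, 1 df | Omnibus, 2 df | Gap (points) |
|---|---|---|---|
| 5.0 | 60.4% | 49.7% | 10.7 |
| 7.93 | 80.0% | 70.6% | 9.4 |
| 10.62 | 90.0% | 83.3% | 6.7 |

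λ = 7.93 corresponds to a group difference of √(7.93 × (1/140 + 1/50)) = 0.46 SD of the within-person contrast. The omnibus test reaches 80% at λ = 9.79, a difference of 0.52 SD or 9.79/7.93 = 1.23 times the sample size. If the same 7.93 were tested on 4 df (for illustration, three levels crossed with three AOIs: 2 × 2), power would be 59%.

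**4. Other shapes.** Write the profile of the group difference over the three levels as (0, a, 1). The share of λ caught by the equal-step contrast is 3 / (4(a² − a + 1)). It is 1 at a = 0.5 and falls to 0.75 at a = 0 or a = 1, its minimum for any non-decreasing profile. With the omnibus test held at 80% (λ = 9.79):

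| Profile of the group difference | Equal-step contrast | Contrast scored 0/5/25 |
|---|---|---|
| Linear (0, 0.5, 1) | 87.6% | 83.7% |
| Proportional to avatars (0, 0.2, 1) | 83.7% | 87.6% |
| Plateau (0, 1, 1) | 76.9% | 53.1% |
| Threshold (0, 0, 1) | 76.9% | 86.4% |
| Inverted U (0, 1, 0) | 5.0% | 17.5% |

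The last row shows the problem of interpretation. A group difference that peaks at five avatars and returns to its starting value gives the omnibus test 80% power, while the equal-step contrast stays at its 5% error rate. The plateau row shows why equal-step scores are safer than avatar counts.

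**The case against.** A journal article condenses the analysis, and contrasts within a repeated-measures factor are often left to an analysis plan that is not shown. The article excludes no contrast and never calls complexity unordered. This stands as a caution: the point is not that detail is absent, but that the one test stated does not match the hypothesis it serves.

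A reader might infer that the plan accepts a non-monotone pattern as support. The document does not say so. It has no decision rule, and its hypothesis names an increase, so a fall would contradict the text whatever the p-value. The most that can be said is that a significant omnibus term could be read as support.

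A reader might also infer that power is lost in general. It is not. The hypothesis predicts an increase, not a straight line; a plateau or threshold also fits it, and there the equal-step contrast is about 3 points weaker than the omnibus test (76.9% against 80%).

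Finally, because AOI is a factor, the three-way term can help to locate an effect in non-social areas. That is correct, but the term does not by itself isolate the non-social claim or its direction.

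**Conclusion.** The concern holds as a mismatch between hypothesis and test. A significant omnibus term does not by itself establish that non-social gaze rises with complexity more in autistic participants; this follows from the structure of the test and needs no assumption about effect size.

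The power cost is conditional. For a near-linear rise on one outcome the omnibus test has about 7 to 11 points less power than the trend contrast over the range examined (71% against 80% in the central case). For plateau or threshold rises it has about 3 points more, which is the worst case for the contrast under any non-decreasing pattern. These figures rest on the assumptions in step 2 of the working, above all on an assumed effect size. The recruitment target was set on eye-region dwell time and is not affected. The point should be settled before the data are analysed, but it touches one hypothesis of three and not the one that sets the sample size.

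**What to change.** In Statistical analyses, state that hypothesis 3 is tested by the group-by-linear-trend contrast over low, moderate and high complexity (scores −1, 0, 1), computed on the non-social AOIs taken together and averaged over the distractor conditions. Name dwell time as the lead measure and apply the same contrast to number of fixations and mean fixation time, since the hypothesis names all three. Keep the test two-sided, and state that support requires the contrast to be significant in the predicted direction. Keep the omnibus MANCOVA as a secondary analysis.

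Report the group difference at each level with its confidence interval. This matters because, with three levels, the equal-step contrast is the change in group difference from low to high: it shows a rise between the ends but not what happens at the middle level.

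The cost is analysis wording only, with no change to recruitment, procedures or data collection. The downsides are about 3 points less power for a plateau or threshold rise, and that non-monotone patterns would be tested only in the secondary analysis.

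### The study is powered for one eye-region dwell-time comparison, but that comparison is neither singled out as primary nor named in the analysis, and about ten hypothesised comparisons share an unadjusted 0.05

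*Protocol article*

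**What the plan says.** All references are to the protocol article.

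- **Sample size calculation.** The study was sized "based on one of the primary hypotheses of detecting a between-group difference in total fixation duration (dwell time) on the eye regions". The phrase implies more than one primary hypothesis; the section does not list them. The inputs are g = 0.47, two-sided 0.05, 80% power and an allocation ratio of 0.35. They give 139 ASC and 48 neurotypical participants, with 140 and 50 to be recruited.
- **Hypotheses.** Three numbered hypotheses, unranked. Each covers more than one gaze metric, and the second covers both social and non-social areas.
- **Outcome measures.** Three fixation metrics on a list of AOIs. No metric or AOI is marked as primary.
- **Statistical analyses.** "MANCOVAs will be conducted with group (ASC vs neurotypical) as the between-subjects factor and AOIs as within-subjects factors". A further MANCOVA adds social complexity, and the ASRS score enters as covariate. The rule on significance is "All statistical tests for significance will be two-tailed and with a significance level alpha set at p < 0.05".

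**The concern.** The comparison that justified the sample size cannot be found in the analysis section. A reader of the results would not know which test the 80% power belongs to. It could be an omnibus group or group-by-AOI test, or an eye-region follow-up contrast.

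In addition, several hypotheses appear to be primary, none is ranked, and one level is set for every test. Under that rule, a significant result on any of the stated metrics and regions could be reported as support for a primary hypothesis. The Discussion hopes to identify behavioural markers of ASC, so it matters whether a positive result comes from the one powered test or from one of about ten.

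**Working it through.** **1. Reproduce the stated sample size.** Inputs, all from Sample size calculation: g = 0.47 (SD = 1), two-sided alpha 0.05, power 80%, ratio 0.35.

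n(ASC) = (1.960 + 0.842)² × (1 + 1/0.35) / 0.47² = 137.05, so 138. Neurotypical: 0.35 × 138 = 48.3. This is within rounding of 139 and 48.

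Power from the noncentral t, with noncentrality 0.47 / √(1/n₁ + 1/n₂):

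| ASC / NT | Noncentrality | Power |
|---|---|---|
| 139 / 48 | 2.807 | 79.8% |
| 140 / 50 | 2.853 | 81.0% |

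The stated N is therefore that of a plain two-sample test of one endpoint, with no covariate and no multiplicity adjustment.

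**2. Effect of the ASRS covariate.** The article gives no group difference in ASRS, so I assume d = 0.5, 0.8 or 1.0 SD and no gaze variance explained by ASRS. With p = 50/190, r² = d²p(1−p) / (1 + d²p(1−p)), and the noncentrality is multiplied by √(1−r²). Power falls from 81% to 79%, 76% or 74%. Any gaze variance that ASRS explains would offset this.

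**3. Count the comparisons (Hypotheses section).**

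| Hypothesis | Metrics and region | Count |
|---|---|---|
| 1 | fixations, dwell time; eyes | 2 |
| 2, social | fixations, dwell time; head and body together | 2 |
| 2, non-social | fixations, mean fixation, dwell time | 3 |
| 3 | the same three metrics, non-social, by complexity | 3 |
| Total | | 10 |

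The total is 12 if head and body are tested separately.

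**4. Chance of at least one false positive, each test at 0.05.** Under independence: 1 − 0.95¹⁰ = 0.401. The article gives no correlations, so I simulated ten equicorrelated normal test statistics (400,000 draws):

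| Assumed correlation | 0 | 0.3 | 0.5 | 0.7 | 0.9 |
|---|---|---|---|---|---|
| Chance of at least one false positive | 40% | 35% | 29% | 21% | 13% |

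If only two or three tests counted as primary, the independent values would be 1 − 0.95² = 9.8% and 1 − 0.95³ = 14.3%.

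**5. Does the 80% carry over to the omnibus test?** Take q uncorrelated AOIs with equal SD, 140/50, no covariate; 140 × 50 / 190 = 36.84.

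- Joint test of group on all AOIs, with only the eye AOI shifted by 0.47 SD: noncentrality 36.84 × 0.47² = 8.14, F on q and 189 − q df. Power is 72%, 65%, 56% and 46% for q = 2, 3, 5 and 8.
- Group-by-AOI test, with the lost eye time moving to one other AOI: noncentrality 36.84 × 2 × 0.47² = 16.28, F on q − 1 and 190 − q df. Power is 96% for q = 3 and 84% for q = 8.

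Omnibus power can thus lie well below or above 80%, depending on AOI coding, on where the lost gaze time goes and on correlations that are not given.

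**6. Choice of remedy.** Bonferroni over all ten (alpha 0.005) would leave eye dwell time with 50.6% power at 140/50; restoring 80% needs about 233 ASC and 82 NT. Naming it as the single primary test at 0.05 keeps 81.0% (before ASRS adjustment).

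**The case against.** **A stronger reading is tempting.** The non-social AOIs include everything left over: "AOIs within non-social stimuli will consist of shopping windows, the ambulance when present, and the remaining background". One might infer that AOI dwell times add up to total fixation time, so that the group effect cannot detect an eye difference and has only 5% power. The documents do not support this. With AOI within subjects, an eye-specific difference shows in the group-by-AOI term, not in the group effect averaged over AOIs. The 5% results from assuming equal totals in both groups, which the article nowhere states. The sum also fails if the head AOI contains the eye, mouth and forehead AOIs, and it has no meaning for mean fixation time.

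**The two halves pull against each other.** If ten contrasts are run, eye dwell time is one of them and its stated power applies. If only omnibus tests are run, there are few tests and 40% is too high. This stands: both worst cases cannot hold at once. But the article leaves open which applies, and naming the primary contrast settles it.

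**The count is a reconstruction.** Sample size calculation does not list the primary hypotheses, and Statistical analyses does not list ten tests. This stands as a limit on the figure.

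**Detail may sit in an analysis plan, and the study is preparatory.** Follow-up contrasts and multiplicity rules are often placed there, and a nominal 0.05 does not by itself exclude adjustment. The hypotheses also fix metrics, regions and directions in advance, and the Abstract speaks only of supporting further research. These points lower the severity. They do not remove the point, which rests on what the article states: one level for all tests, and a sample size built on "one of" several primary hypotheses.

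**Conclusion.** The point holds in a limited form. The sample size is arithmetically right for a two-group comparison of eye-region dwell time, and the 80% power belongs to that contrast. The plan neither makes it the primary test nor names it among its analyses, and the power of the omnibus MANCOVA cannot be derived from the article.

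Under the stated rule, the chance of at least one false positive exceeds 5%. It is about 40% at most, and 35% to 13% for assumed correlations of 0.3 to 0.9. These figures assume that all three hypotheses are primary and that each stated comparison is tested once. The metrics are probably positively correlated, so 40% is an upper illustration and not an estimate.

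A reader might infer that neither the 80% nor the 5% means anything for this study. That goes too far: both are valid for the eye-dwell contrast once it is singled out. The change is worth making because it alters what the study may conclude, but it is not a fatal defect.

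**What to change.** In Statistical analyses:

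1. Name the group difference in eye-region dwell time, averaged over the six scenarios and taken from the planned ASRS-adjusted model, as the single primary contrast at two-sided 0.05.
2. Label the other nine comparisons in Hypotheses as secondary and test them with Holm correction.
3. Describe the omnibus MANCOVA tests as supportive.
4. Limit the general 0.05 statement accordingly, and change Sample size calculation so that eye-region dwell time is the primary hypothesis and not one of several.

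This should be settled before group comparisons are run. It changes wording only and needs no further participants. The primary contrast keeps 81% power before ASRS adjustment (74% to 79% under the ASRS assumptions above).

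The cost falls on the secondary comparisons. Holm's first step uses 0.05/9 = 0.0056. At that level a two-group effect of 0.47 has power between 51% (at 0.005) and 54% (at 0.00625), and later steps are less strict.
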